## Abstract

**Background:**

Deep-brain stimulation targeting the subthalamic nucleus (STN) can be used to treat motor symptoms and dyskinesia in the advanced stages of Parkinson’s disease (PD). High-frequency stimulation (HFS) of the STN can lead to consistent, long-term improvement of PD symptoms. However, the effects of HFS on the axial symptoms of PD, specifically freezing of gait, can be limited or cause further impairment. While this can be alleviated via relatively low-frequency stimulation (LFS) in selected patients, LFS does not control all motor symptoms of PD. Recently, the National Engineering Laboratory for Neuromodulation reported preliminary findings regarding an efficient way to combine the advantages of HFS and LFS to form variable-frequency stimulation (VFS). However, this novel therapeutic strategy has not been formally tested in a randomized trial.

**Methods/design:**

We propose a multicenter, double-blind clinical trial involving 11 study hospitals and an established deep-brain stimulation team. The participants will be divided into a VFS and a constant-frequency stimulation group. The primary outcome will be changes in stand–walk–sit task scores after 3 months of treatment in the “medication off” condition. Secondary outcome measures include specific item scores on the Freezing of Gait Questionnaire and quality of life. The aim of this trial is to investigate the efficacy and safety of VFS compared with constant-frequency stimulation.

**Discussion:**

This is the first randomized controlled trial to comprehensively evaluate the effectiveness and safety of VFS of the STN in patients with advanced PD. VFS may represent a new option for clinical treatment of PD in the future.

**Trial registration:**

ClinicalTrials.gov, NCT03053726. Registered on February 15, 2017.

## Background

Deep-brain stimulation (DBS) of the subthalamic nucleus (STN) is an established treatment for Parkinson’s disease (PD). However, debilitating axial symptoms such as gait impairment, postural instability, postural abnormalities, dysphagia, and dysarthria are frequently observed in individuals with advanced PD [1]. Axial motor impairments can be highly debilitating and are a common cause of disability in patients with PD. Freezing of gait (FOG) is a unique and disabling clinical phenomenon that typically occurs when initiating gait or when turning while walking. FOG is characterized by brief episodes in which the patient demonstrates an inability to step, or makes repeated use of extremely short steps [2]. The inability to start walking is a prominent feature in PD patients with FOG. However, once this so-called ‘freezing’ pattern is interrupted, patients often regain the ability to walk normally [3]. FOG has also been observed in patients with progressive supranuclear ophthalmoplegia, multiple system atrophy, corticobasal degeneration, and numerous other diseases [4]. Additional axial signs include postural instability and changes in postural alignment, such as camptocormia or Pisa syndrome. Dysphagia and speech disorders, especially dysarthria and stuttering, are equally disabling axial motor features. However, conventional DBS stimulation has limited therapeutic potential for treating these symptoms. Thus, these symptoms represent a public health issue for which a specific treatment is currently lacking.

High-frequency DBS of the STN (STN-HFS) mainly improves levodopa-sensitive PD symptoms. However, it is typically less effective in improving axial symptoms, such as FOG [5]. Previous studies have shown that low-frequency subthalamic stimulation (STN-LFS) improves axial motor activity in some PD patients, but with short-term therapeutic efficacy. Thereafter, patients may present with increased tremor, rigidity, and bradykinesia, and the intensity of symptoms often outweighs the initial benefits of LFS therapy for FOG [6, 7]. The conventional HFS or LFS programming is called constant-frequency stimulation (CFS) due to the fixed stimulation frequency and is the current standard method of DBS. Previously, we successfully used variable-frequency stimulation (VFS) of the STN to treat FOG in patients with PD [8]. Furthermore, we recently conducted a study with 28 participants (under review) that revealed that, compared with HFS and LFS, VFS DBS improved FOG and appendicular motor symptoms in patients with PD, with sustained benefits for 12 months. Our pilot study suggested that VFS composed of both HFS and LFS was safe, and we did not observe any clinically relevant neuropsychiatric adverse effects. To the best of our knowledge, no controlled prospective studies have compared VFS with CFS in patients with PD. To this end, we designed a prospective, controlled study investigating the outcome of VFS in patients with advanced PD.

### Aims

The motives for this clinical study are twofold. First, we plan to evaluate the short-term effects of VFS and CFS on motor and axial symptoms in patients with advanced PD. Second, we hope to gain insight regarding whether VFS is more effective than CFS after 3 months of treatment, with a 6-month follow-up period. The study has a randomized, double-blind design.

## Design and methods

### Trial design

The RESTEP study (ClinicalTrials.gov, NCT03053726) is a double-blind, randomized, multicenter trial designed to evaluate the safety and effectiveness of STN-VFS treatment in participants with advanced PD. According to the trial flow chart (Fig. 1), participants with advanced PD who had previously undergone DBS will be screened based on strict inclusion and exclusion criteria. A total of five follow-up surveys will be scheduled as shown in Table 1. After recruitment, pulse generators previously implanted in all participants will be upgraded from those with a single mode (CFS only) to those that are capable of dual-mode stimulation (CFS or VFS). Following this upgrade, participants will be randomly and equally divided into two groups: the CFS group and the VFS group. After 3 months of stimulation under the blinded conditions, all participants will receive VFS and follow-up assessments for 6 months. The protocol design is based on the guidelines of the Consolidated Standards of Reporting Trials and Standard Protocol Items: Recommendations for Interventional Trials (SPIRIT) (see Additional file 1), and the study results will also be reported according to these guidelines. Informed consent will be obtained from all participants in accordance with the policies of the board.

**Fig. 1 Fig1:**
[figure not shown]
Flow chart of the RESTEP trial

**Table 1 Tab1:** Detailed schedule of the RESTEP trial

Schedule	Baseline		Visit		
	Screening	Upgrading	EG for VFS, CG for CFS	EG for VFS, CG for VFS	EG for VFS, CG for VFS
Time	3 ± 2 days	5 ± 2 days	90 ± 14 days	90 ± 14 days	180 ± 14 days
Follow-up	V1	V2	V3	V4	V5
Informed consent	X				
Criteria for inclusion	X				
Criteria for exclusion	X				
MMSE	X		X		X
Hoehn-Yahr staging	X				
Medical history/demographic data	X				
Physical examination	X				
Records of side effects	X	X	X		X
PDQ-39	X		X		X
FOG-Q	X		X		X
GAFQ	X		X		X
Medication	X		X		X
UPDRS (part I/II/IV)	X		X		X
Upgrade to dual mode		X			
Random grouping		X			
Programming	X	X	X	X	X
SWS test	X	X	X	X	X
UPDRS (part III)	X	X	X	X	X
Admission confirmed	X				
AE		X	X	X	X
SAE		X	X	X	X

*AE* adverse event, *CFS* constant-frequency stimulation, *CG* control group, *EG* experimental group, *FOG-Q* Freezing of Gait Questionnaire, *GAFQ* Gait and Falls Questionnaire, *MMSE* Mini-Mental State Examination, *PDQ-39* Parkinson’s Disease Questionnaire-39, *SAE* serious adverse event, *SWS* stand–walk–sit, *UPDRS* Unified Parkinson’s Disease Rating Scale, *VFS* variable-frequency stimulation

### Patient population and recruitment

We intend to enroll a total of 106 participants aged over 18 years. The prospective cohort will comprise patients with PD who have received STN-DBS treatment and have implanted impulse generators that are compatible with VFS (PINS Medical).

#### Inclusion criteria

The inclusion criteria are as follows:
Patients with idiopathic PDAged ≥18 years of either sexPatients who have already undergone DBS and currently have an implanted STN-DBS stimulatorA Mini-Mental State Examination score ≥24A Hoehn-Yahr score ≥2.0 when undergoing CFS in a “medication off” stateA score ≥1 on the 14-item Unified Parkinson’s Disease Rating Scale II (UPDRS-II)A score ≥2 on the 15-item UPDRS-IIThe ability to walk ≥10 m independently when receiving CFS in a “medication off” state

#### Exclusion criteria

The exclusion criteria are as follows:
Pregnant women, breastfeeding mothers, or woman who are unable to take effective measures to prevent pregnancyPresence of other diseases that can affect walking distance, such as joint disease in the lower body, spinal disease, neuropathy, or serious heart or lung diseaseSerious health conditions such as tumor, liver or kidney disease, and so forthEpilepsy or other seizure disordersMental disorders or dementiaInability to comprehend the experimental protocol or voluntarily provide informed consentLack of cooperation with follow-up requirementsAdditional reasons for exclusion at the discretion of the clinical investigator

#### Recruitment of participants

Participants will be recruited by placing advertisements on social media and posters in clinics and directly at the participating centers. The recruitment information mainly includes eligibility criteria and contact details. A well-trained investigator in each participating center will be responsible for screening all potentially eligible patients based on the eligibility criteria and obtaining the informed consent.

### Interventions

#### Constant-frequency stimulation

To deliver CFS, electrical stimulation will be set to a constant frequency by the physician programming the stimulation frequency parameters (i.e., the pulse width and amplitude). The participants with receive STN-DBS with single-frequency, single pulse width, and single-amplitude stimulation.

#### Variable-frequency stimulation

The VFS parameters will be selected based on previous findings regarding the relationship between stimulation frequency and movement rhythm regulation in humans. The stimulation frequency will be set to alternate between high and low frequencies.

#### Concomitant interventions

Participants will be allowed to continue taking pretrial medications. Use of all drugs, if any, will be documented in the case report form (CRF).

### Randomization and blinding

Eligible participants will be randomly assigned to one of two groups (CFS group or VFS group) after completing the baseline measurements. A 1:1 assignment sequence (based on computer-generated random numbers) will be produced by The Peking University Clinical Research Institute. The computer-generated random numbers will be used to create the participant numbers and order lists, which will be placed in opaque sealed envelopes and sent to the research centers. The research clerk will keep copies of the order lists and participant numbers.

Throughout the study, with the exception of the study programmer, all participants and study staff (including investigators, trainers, and statisticians) will be blinded to the treatment allocation. Independent raters who have no therapeutic relationships with the participants and who are blind to the treatment conditions will conduct outcome assessments. The independent raters will be clinical neurologists who have received additional training on the use of the outcome assessments, had the opportunity to listen to conducted assessments, and received direct feedback regarding their assessments from supervisors. Furthermore, the Data and Safety Monitoring Board (DSMB) will review a random selection of 20% of the recorded assessments. Loss of blinding may occur due to the magnitude of the therapeutic effect or any other subjective perception that indicates that VFS or CFS is delivered.

### Trial outcomes

#### Primary clinical outcomes

The primary outcome will be stand–walk–sit (SWS) task scores at 3 months compared with the baseline scores. The domain of the SWS score is the gait. The study will compare the mean scores in each group between 3 months and baseline, using the mean scores from each group. The SWS test is a simple and quick functional mobility test that requires an individual to stand up, walk 5 m, turn, walk back, and sit down. The time taken to complete the test is strongly correlated with the level of functional mobility. This test will be videotaped and scored by two blinded neurologists.

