#### Secondary clinical outcomes

As secondary outcomes, we will use the Freezing of Gait Questionnaire, Gait and Falls Questionnaire, and Parkinson’s Disease Quality of Life questionnaire, as well as total UPDRS and UPDRS-III scores to assess PD symptom severity at 3 and 6 months compared with the baseline. These questionnaires assess physiological symptoms and emotional function in patients with PD. Participants in both trial groups will be asked to complete these questionnaires at baseline and post-treatment, and the trial group will also be asked to complete the measures 3 months and 6 months post-treatment. The study will compare the mean change scores from baseline at each time point, using the mean scores from each group.

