#### Data analysis

All evaluations of effectiveness and safety will be conducted according to the intention-to-treat principle. The final data will be analyzed using IBM SPSS 13.0 or higher (SPSS, Inc., Chicago, IL, USA) and SAS 9.4 or higher (SAS Institute Inc., Cary, NC, USA). A *p* value <0.05 will be considered statistically significant. Data will be analyzed with *t* tests and χ^2^ tests for continuous variables and categorical variables, respectively.

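### The primary comparison is worded as 3 months against baseline within each group, so the stated analysis does not specify a test of VFS against CFS

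*Protocol article*

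**What the plan says.** Under Primary clinical outcomes, the endpoint is defined against baseline: "The primary outcome will be stand–walk–sit (SWS) task scores at 3 months compared with the baseline scores". The comparison is then described as follows: "The study will compare the mean scores in each group between 3 months and baseline, using the mean scores from each group". The abstract calls the same endpoint a change and fixes the medication state: "The primary outcome will be changes in stand–walk–sit task scores after 3 months of treatment in the “medication off” condition".

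Under Data analysis, the method is one sentence: "Data will be analyzed with *t* tests and χ^2^ tests for continuous variables and categorical variables, respectively". It does not say which kind of t test and mentions no covariate.

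The question the trial asks is between arms. The Aims section wants to learn "whether VFS is more effective than CFS after 3 months of treatment". The Sample size section starts from a pilot difference of at least 20% between VFS and CFS on SWS, and sets 53 per group to detect a difference between the treatments.

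The sentence for the secondary outcomes is built differently: "The study will compare the mean change scores from baseline at each time point, using the mean scores from each group". It names change scores as the quantity compared. The primary sentence does not.

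**The concern.** A contrast has to name what is compared with what. The primary sentence names two time points and places the comparison inside each group; it does not set VFS against CFS. A paired t test run separately in each arm would fit both that sentence and the Data analysis section, yet would not answer the question in the Aims.

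The stake is the primary conclusion. If one arm's change is significant and the other's is not, that does not show that the arms differ. Change shared by both arms is plausible here: the Sample size section allows for a placebo effect, every participant has the generator upgraded, and programming is scheduled at every visit. The section on blinding also accepts that blinding may be lost.

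A smaller matter is precision. Baseline SWS is already collected, and a t test on change makes less efficient use of it than a model with baseline as covariate.

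**Working it through.** **Inputs from the protocol article.** 53 per group, 10% attrition, 1:1 allocation, two-sided 5% level. The Sample size section gives power as both 80% and 90%, so both are carried. No SD for SWS and no baseline-to-3-month correlation are given.

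**The plan's own figure.** Without an SD, 53 per group cannot be reproduced. Net of attrition it is 53 × 0.9 = 47.7, about 48 evaluable per arm. The standardized difference this implies for a two-sample comparison is d = √(2/48) × (1.960 + z_power):
- 90% power: 0.2041 × (1.960 + 1.282) = 0.66
- 80% power: 0.2041 × (1.960 + 0.842) = 0.57

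**Step 1: the literal within-group reading.** Let both arms have the same true standardized change s (mean change divided by the SD of change), so there is no treatment difference. Each within-arm test is significant with probability

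p = Φ(s√48 − 1.96) + Φ(−s√48 − 1.96).

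The arms are independent, so P(VFS significant, CFS not) = p(1 − p). This is largest at p = 0.5, where it equals 0.25; that occurs at s = 1.96/√48 = 0.283.

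| s | p | p(1 − p) |
|---|---|---|
| 0 | 0.050 | 0.048 |
| 0.2 | 0.283 | 0.203 |
| 0.283 | 0.500 | 0.250 |
| 0.4 | 0.791 | 0.165 |
| 0.5 | 0.934 | 0.062 |

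A direct two-sided 5% test between arms would wrongly favour VFS 2.5% of the time (0.05/2), whatever the shared change.

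**Step 2: the between-arm reading.** With equal variance σ² at both times and correlation rho:
- change score: 2σ²(1 − rho)
- ANCOVA: σ²(1 − rho²)
- ratio: (1 − rho²) / [2(1 − rho)] = (1 + rho)/2

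With 48 per arm, take an effect that gives the change-score t test its planned power. Dividing d by √((1 + rho)/2) then gives the ANCOVA power:

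| Assumed rho | Variance ratio | From 80% | From 90% |
|---|---|---|---|
| 0.5 | 0.75 | 89.9% | 96.3% |
| 0.7 | 0.85 | 86.0% | 94.0% |

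Both tests are valid under randomization; the difference is precision only.

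**The case against.** The best defence is that the between-arm intent is plain elsewhere. The abstract says VFS is compared with constant-frequency stimulation, the Aims ask whether VFS is more effective, and the sample size rests on a difference between treatments. The primary sentence could be a loose way of saying that mean changes are compared between groups, as the secondary-outcome sentence suggests. Nowhere does the article say a conclusion will rest on one arm being significant and the other not. The article is also condensed, and covariates are commonly left to the analysis plan.

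Much of this stands. A reader might infer that the trial has no VFS-versus-CFS test at all; the documents do not support that, because the intent is stated in several places. A reader might also infer that baseline SWS is discarded. It is not: a paired test or a t test on change uses it, and no section specifies a t test on 3-month scores alone. Leaving out ANCOVA is not an error of validity.

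What does not stand is that the intent repairs the analysis. Aims and a sample-size target do not define a contrast. The article does state one for the primary outcome, on the wrong axis, and its one sentence on methods does not correct it. This is wording the article fixes badly, not detail it left for later.

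**Conclusion.** The point holds as a mismatch between the stated primary comparison and the trial's aim. As worded, the analysis does not specify a test of VFS against CFS.

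If the wording were followed literally, a finding in favour of VFS alone could arise in up to 25% of trials with no treatment difference. That is a ceiling. It assumes independent arms of 48 with equal change and about 50% power in each, and a decision rule that the article does not state. If a two-sample t test on change is meant, the inference is valid and the cost is precision: at an assumed rho of 0.5 to 0.7, about 4 to 10 percentage points of power relative to ANCOVA.

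Two further inferences are not supported. The 20% planning difference does not contradict a comparison of mean scores, since a percentage of a reference mean converts to a raw difference and the article does not say how it entered the calculation. Nor does the text show a need for a centre factor or for log-transformed times. No defect tied to centre is stated, and the scale of the SWS score is not settled: completion time is mentioned, but the test is also scored from video.

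**What to change.** Replace the comparison sentence under Primary clinical outcomes, and align Data analysis with it, along these lines: the primary analysis is the VFS minus CFS difference in mean SWS at 3 months (V3, medication off), estimated by ANCOVA with baseline SWS as covariate, reported with a two-sided 95% confidence interval and tested at alpha 0.05; changes within each group are reported descriptively only.

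Table 1 schedules SWS at both V1 and V2, so the sentence should also name which pre-randomization assessment is the baseline.

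The cost is a sentence or two. SWS at baseline and at V3 is already scheduled for all participants, so no visits, data or participants are added.

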#### Secondary clinical outcomes

As secondary outcomes, we will use the Freezing of Gait Questionnaire, Gait and Falls Questionnaire, and Parkinson’s Disease Quality of Life questionnaire, as well as total UPDRS and UPDRS-III scores to assess PD symptom severity at 3 and 6 months compared with the baseline. These questionnaires assess physiological symptoms and emotional function in patients with PD. Participants in both trial groups will be asked to complete these questionnaires at baseline and post-treatment, and the trial group will also be asked to complete the measures 3 months and 6 months post-treatment. The study will compare the mean change scores from baseline at each time point, using the mean scores from each group.

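### The 6-month group comparison, and any safety comparison by randomised arm that counts events after the 3-month switch, is not VFS versus CFS, because every control participant is on VFS by then

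*Protocol article*

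**What the plan says.** All places are in the protocol article.

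- **Aim (abstract, Methods/design):** "The aim of this trial is to investigate the efficacy and safety of VFS compared with constant-frequency stimulation".
- **Trial design:** "After 3 months of stimulation under the blinded conditions, all participants will receive VFS and follow-up assessments for 6 months".
- **Table 1:** the V3 column is headed "EG for VFS, CG for CFS". The V4 and V5 columns are both headed "EG for VFS, CG for VFS". The time row gives 90 ± 14 days for V3, 90 ± 14 for V4 and 180 ± 14 for V5. AEs and SAEs are collected at V2 through V5.
- **Secondary clinical outcomes:** the questionnaires and UPDRS scores are used "to assess PD symptom severity at 3 and 6 months compared with the baseline", and then: "The study will compare the mean change scores from baseline at each time point, using the mean scores from each group".
- **Data analysis:** "All evaluations of effectiveness and safety will be conducted according to the intention-to-treat principle". Neither this sentence nor the rest of the section separates the time before the switch from the time after it.

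**The concern.** The aim is a comparison of two stimulation modes, but the two arms receive different modes only up to V3. The secondary analysis nevertheless gives 6 months the same group comparison as 3 months.

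Two misreadings could follow:

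- **Efficacy.** A small or null 6-month difference could be taken as loss of the VFS benefit when it may only show that controls caught up after switching.
- **Safety.** If events after V3 are counted by randomised arm, events that occur on VFS in control participants count on the CFS side. For a new stimulation mode, a bias towards no difference is the unfavourable direction.

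**Working it through.** **Step 1. Stimulation received at each analysis time (Trial design, Table 1).**

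| Time | Experimental group | Control group | What a comparison by arm estimates |
|---|---|---|---|
| V3, 3 months | VFS | CFS | VFS versus CFS |
| V4 | VFS | VFS | early versus delayed VFS |
| V5 | VFS | VFS | early versus delayed VFS |

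The 6 months may be counted from baseline or from the switch. Either way they fall after the switch, when by design no control participant is on CFS. In Table 1 FOG-Q, GAFQ and PDQ-39 are taken after baseline only at V3 and V5, so for these three one of the two post-baseline comparisons is affected.

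**Step 2. Size for efficacy (illustration).** The article states 53 per group, 10% attrition, a 5% level and, in its final sentence on sample size, 90% power. It gives no SD, so the 53 cannot be reproduced, and it is not in dispute here. Evaluable per arm: 53 × 0.90 = 47.7, about 48. The standardised effect detectable with 90% power is (1.960 + 1.282) × √(2/48) = 0.662.

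Assume a secondary outcome had that effect at 3 months and a fraction f of it remained between arms at 6 months. In the normal approximation, power ≈ Φ(3.242f − 1.960):

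- f = 0.50: Φ(−0.34), about 37%
- f = 0.25: Φ(−1.15), about 13%
- f = 0 (complete catch-up): rejection at the 5% level only

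**Step 3. Size for safety (illustration).** Assume a constant adverse event rate in each mode, a true VFS:CFS rate ratio RR, 90 days of CFS in controls, and all events over T days counted by randomised arm. Expected events per person are proportional to RR × T in the VFS arm and to 90 + RR × (T − 90) in the control arm. Hence

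apparent ratio = RR × T / (90 + RR × (T − 90)).

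T = 180 if V5 is counted from the start of randomised stimulation, and T = 270 if it is counted from the switch (90 + 180).

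| True RR | T = 180 | T = 270 |
|---|---|---|
| 1.5 | 270/225 = 1.20 | 405/360 = 1.13 |
| 2.0 | 360/270 = 1.33 | 540/450 = 1.20 |
| 3.0 | 540/360 = 1.50 | 810/630 = 1.29 |

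CFS makes up 90/180 = 50% or 90/270 = 33% of control-arm time.

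**Step 4. Two wording points that bear on this.**

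- *Time origin.* If V4 and V5 are counted from the switch, V5 at 180 days matches the 6 months of VFS follow-up in Trial design. If they are counted from the start of randomised stimulation, V3 and V4 share one window although controls are on different modes, and V5 leaves only 180 − 90 = 90 days after the switch. Table 1 does not say which applies.
- *Who is measured at 6 months.* One sentence in Secondary clinical outcomes assigns the 3- and 6-month measures to the trial group, while Table 1 schedules V5 without distinguishing the groups.

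**The case against.** The strongest reply is that the trial's main question is untouched. The primary outcome is at 3 months, Aims ties the question of whether VFS is more effective to 3 months, and no sentence calls the 6-month contrast VFS versus CFS. A comparison of early with delayed VFS by randomised arm is also a legitimate intention-to-treat contrast. All of this stands. It removes any case for dropping the 6-month p values, but not the need to say what they test.

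The sentence on secondary outcomes could also be read as within-group change, and the assignment of the 6-month measures to the trial group might mean that no group comparison is planned then. This is possible, but comparing change scores using each group's mean reads more naturally as between groups, and Table 1 schedules V5 for both arms. The ambiguity is itself a reason to clarify.

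Three stronger readings are tempting and are not supported:

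- *The plan pools all safety data.* A reader might infer this from the intention-to-treat sentence, but pooling is not spelled out. Table 1 records events visit by visit, and an analysis plan that is not shown could split them by period. The ratios above apply only if pooling occurs; the article gives no adverse event rates and plans χ² tests for categorical variables, not rate ratios.
- *Blinding is wrongly claimed for the whole study.* Randomization and blinding does say "Throughout the study, with the exception of the study programmer, all participants and study staff", but it concerns blinding to allocation. The original arm can stay concealed after everyone moves to VFS, and Trial design ties the blinded stimulation to the first 3 months.
- *Table 1 contradicts Trial design.* It does not if V4 and V5 are counted from the switch. Nor does any rule select the 90-day value by window, so using a V4 walk test in place of V3 would be a slip in execution, not something that the plan prescribes.

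**Conclusion.** The point holds in a limited form and should be fixed; it does not put the trial's main result at risk. The text fixes both the switch of all controls to VFS and a 6-month comparison by group, so that comparison is early versus delayed VFS and cannot serve the stated aim. The safety part is conditional: only a comparison by randomised arm that includes post-switch events is diluted. Under constant rates and full pooling, a true ratio of 2.0 would then appear as 1.33 or 1.20, depending on the time origin of V5. The efficacy figures rest on an assumed 3-month effect and an assumed retained fraction; the rejection rate falls to 5% only with complete catch-up. The primary comparison, the 3-month secondary comparisons and safety comparisons confined to the first 3 months remain valid contrasts of VFS with CFS.

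**What to change.** 1. State that VFS-versus-CFS inference, for efficacy and safety, covers randomisation through V3, with V3 assessments completed before the control group is switched.
2. Label any later comparison by randomised arm as early versus delayed VFS, and add within-person change since starting VFS.
3. Tabulate adverse events separately for the blinded period and the open VFS period, by stimulation received.
4. Reconcile Trial design with Table 1 by giving the time origin of V4 and V5.
5. State in Secondary clinical outcomes whether control participants complete the 6-month measures.

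The cost is plan wording and table layout. No visit, data item or participant is added, and the 6-month comparison by arm can stay under its correct label.
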